### Predefined subgroup-analysis

With respect to the primary outcome a predefined subgroup-analyses will be performed:

▪ rt-PA treatment < 2 hours versus 2-3 hours versus > 3 hours from symptom onset Effectiveness of IV thrombolysis declines over time from symptom onset probably caused by an increase in clot stability. Regarding clot dissolution and reocclusion the beneficial effect of adding antiplatelet therapy might therefore be different over time. The risk of bleeding can also change over time [2].

▪ trial medication within 1 hour versus between 1-1.5 hours from rt-PA bolus. Reocclusion occurs at a median time of 65 minutes after start of rt-PA treatment. Administration of Aspegic in the first hour after the start of rt-PA treatment is therefore expected to result in better outcome [6].

▪ based on ethnicity differences: whites versus blacks, whites versus Hindu's, whites versus blacks and Hindu's, Hindu's versus the other ethnic groups. Previous studies on thrombolytic therapy in acute myocardial infarction suggest that racial differences do exist with an increased thrombolytic effect in blacks accompanied by an increased risk of bleeding complications. The beneficial or detrimental effect of the addition of antiplatelet therapy to IV rt-Pa might therefore differ among different ethnic groups [24-26].

Subgroup analyses consist will consist of a simple comparison of these different groups on primary and secondary outcome measures.

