## Methods and Design

### Study design and objective

The Antiplatelet therapy in combination with Recombinant t-PA Thrombolys in Ischemic Stroke (ARTIS) Trial is a multi-center, prospective open, randomised controlled trial with blind endpoint assessment (PROBE-design). We compare direct addition of 300 mg aspirin to intravenous rt-PA thrombolysis for ischemic stroke versus standard thrombolysis care, in which antiplatelet drugs are usually delayed by 24 hours after rt-PA. All participating centres are experienced in thrombolytic treatment for acute stroke.

The primary objective of the ARTIS-Trial is to investigate whether the addition of asprin to standard rt-PA thrombolysis reduces poor outcome in acute ischemic stroke. Poor outcome is defined as death or dependency assessed by the modified Rankin Scale (mRS, score 3-6) at 3 months follow-up.

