### Enrolment procedures

The study population are acute ischemic stroke patients who present at participating centres and are treated with intravenous (IV) thrombolysis with rt-PA. Patients aged 18 years or older can be enrolled. Patients will be asked for written informed consent. The trial itself has no other firm exclusion criteria than those established by the judgment of the individual treating physician using local protocols for IV rt-PA treatment. When the patient has a diminished decision-making capacity as result of the stroke (e.g. aphasia), informed consent will be obtained from a representative of the patient. Exclusion of these patients would lead to a selective patient sample. Patients are also excluded if they have:

▪ known antiplatelet therapy in the previous 5 days (in case of uncertainty the patient may be included);

▪ known thrombocytopenia or thrombocyte count < 100 * 10E9/l;

▪ known contra-indications to acetylsalicylic acid treatment;

▪ known anticogualant therapy in the previous 5 days;

▪ known legal incompetence of the patient prior to this stroke.

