### Intervention

In order to prevent delay of start of thrombolytic treatment, informed consent and randomisation procedures will be performed as soon as continuous infusion of rt-PA (0.9 mg/kg) has started after bolus administration (10%) Patients allocated to the active group will receive 300 mg aspirin (Aspégic^®^) as lysine salt intravenous as bolus. Since there is a peak in platelet activation after 2 hours after initiation of rt-PA thrombolysis [10], aspirin will be administered within 1.5 hours after the rt-PA bolus. Patient and treating physician are not blinded for treatment allocation.

We choose to apply aspirin intravenously for two reasons. First, onset of action has to be as soon as possible as re-occlusion starts to occur soon after rt-PA administration [6,7]. Intravenous aspirin leads to faster platelet suppression than oral aspirin, which results in a widely varying uptake [20]. Aspirin may be given simultaneous with the rt-PA continuous infusion, preferably through a different intravenous line. In case of only one intravenous access, rt-PA infusion has to be shortly interrupted in order to administer aspirin through this line with saline flushing before and afterwards.

Second, intravenously administration enables patients having swallowing difficulties caused by their stroke to be included. Exclusion of this subgroup would make the trial prone to inclusion bias.

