### Data collection

At baseline following patient characteristics are collected at each participating site: age, sex, ethnicity, medical history, pre-stroke medication, pre-stroke mRS, blood pressure, Glasgow Coma Scale (GCS), National Institutes of Health Stroke Scale (NIHSS), time of symptom onset, rt-PA bolus and (if applicable) trial medication, thrombocyte count and coagulation-International Normalized Ratio. Baseline CT-scans will be collected from participating centres and assessed blindly centrally at the coordinating centre for dens media sign, early ischemic changes and degree of leukoariosis by an independent blinded neuro-radiologist.

At follow-up, neurological deficits are assessed by the NIHSS at 7-10 days or at discharge, if this is before 7 days. Clinical deterioration, defined as a 4 or more points increase on the NIHSS, will be followed by CT-scan and registration as (serious) adverse events including possible cause by each participating site. This CT-scan will be assessed at the coordinating centre as well.

Primary outcome will be assessed by a blind research nurse from the clinical trial office of the coordinating centre, who will score the mRS by telephone using a structured interview. To increase the inter-observer reliability the number of research nurses will be limited to a maximum of three. Disability will be assessed by the same research nurse during the same telephone interview using the Amsterdam Linear Disability Scale [22]. See Additional file 1 for all data collection forms.

In patients with a poor outcome at three months, the Data Collection Committee composed of the investigators of the coordinating centre and the local investigator, judges whether this poor outcome is attributed to the initial ischemic stroke, reported adverse event or other causes.

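### The early-versus-late aspirin subgroup is defined by a post-randomisation event that only the aspirin arm can have, so its planned comparison is not randomised

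*Protocol article*

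**What the plan says.** The section on predefined subgroup analysis names three factors for the primary outcome. The second is "trial medication within 1 hour versus between 1-1.5 hours from rt-PA bolus". The rationale is the timing of re-occlusion, about 65 minutes after rt-PA is started, and the article states that dosing in the first hour should give better results. The section closes by planning a plain comparison of the subgroups on primary and secondary outcomes. It mentions no adjustment and no interaction test.

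Four other statements bear on this:

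- Intervention, on sequence: "informed consent and randomisation procedures will be performed as soon as continuous infusion of rt-PA (0.9 mg/kg) has started after bolus administration".
- Intervention, on who is dosed: "Patients allocated to the active group will receive 300 mg aspirin". The trial is open to patient and treating physician.
- Study design and objective, on the comparator: "standard thrombolysis care, in which antiplatelet drugs are usually delayed by 24 hours after rt-PA". No placebo is described.
- Data collection, on the times recorded: "time of symptom onset, rt-PA bolus and (if applicable) trial medication".

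For patients whose stroke has impaired their capacity, Enrolment procedures says that "informed consent will be obtained from a representative of the patient".

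**The concern.** A subgroup analysis of a randomised trial asks whether the treatment effect differs between levels of a factor. Both arms must have a value for that factor, and allocation must not influence it. Bolus-to-aspirin time meets neither condition. It becomes known only after allocation, and it does not exist for controls.

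What remains is early-dosed against late-dosed aspirin patients. Those groups were formed by circumstances at the bedside, not by randomisation. Any difference in outcome mixes a timing effect with whatever made some patients receive the drug sooner. Because the analysis is labelled predefined and comes with a directional hypothesis, a difference in the expected direction could be read as confirmation that timing matters when it is only a difference in case mix.

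**Working it through.** **1. Which patients have a value for the factor?**

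| Subgroup factor | When fixed | Aspirin arm | Control arm |
|---|---|---|---|
| Symptom onset to rt-PA bolus | Before randomisation; also a stratification factor | Yes | Yes |
| Ethnicity | Before randomisation | Yes | Yes |
| rt-PA bolus to trial medication | After randomisation | Yes, if dosed | No |

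The third row follows from Intervention (bolus, then consent and randomisation, then aspirin in the active arm only) and from Data collection (time recorded only where it applies). Comparing each aspirin timing group with all controls does not help, because no control subgroup matches either one. An aspirin-arm patient who was never dosed, or was dosed after 1.5 hours, would fall in neither category.

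**2. Could the timing groups differ in prognosis?**

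Consent falls between bolus and aspirin. Where the stroke has impaired capacity, a representative must be found and asked. This could delay aspirin in more severely affected patients, but the article does not say how long it takes. Severity is not a stratification factor, and stratification would not balance timing groups within one arm anyway.

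**3. The plan's own figures.**

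Inputs from Trial size: 0.50 v 0.40 poor outcome, two-sided 0.05, 80% power, 400 per group. The usual two-proportion formula gives 388 per group, or 408 with continuity correction. Power at 400 is 81.3%, or about 79.3% with the correction. The 95% half-width is 1.96 × √(0.25/400 + 0.24/400) = 0.0686, stated as 0.069. The sample size reproduces and this point does not touch it.

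**4. How large could a spurious timing difference be?**

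The article gives no figure for this contrast, so every input here except the arm size (400) and the 40% overall risk is an assumption. The aspirin arm is split 200/200, there is no true timing effect, and half of the patients are severe strokes. The spurious difference is

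(severe share late − severe share early) × (risk if severe − risk if mild).

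The chance of p < 0.05 uses the normal approximation with 200 per group.

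| Severe share, early v late | Risk mild / severe | Poor outcome, early v late | Difference | Chance of p < 0.05 |
|---|---|---|---|---|
| 50% v 50% | either pair below | 40% v 40% | 0 | 5% |
| 45% v 55% | 20% / 60% | 38% v 42% | 4 points | 13% |
| 40% v 60% | 20% / 60% | 36% v 44% | 8 points | 37% |
| 35% v 65% | 20% / 60% | 34% v 46% | 12 points | 69% |
| 45% v 55% | 25% / 55% | 38.5% v 41.5% | 3 points | 9% |
| 40% v 60% | 25% / 55% | 37% v 43% | 6 points | 23% |
| 35% v 65% | 25% / 55% | 35.5% v 44.5% | 9 points | 45% |

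Example, third row: (0.60 − 0.40) × (0.60 − 0.20) = 0.08. If the more severe patients are dosed sooner, the shares swap and every sign reverses.

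Precision is also low. With 200 v 200 the half-width is 1.96 × √(0.24/200 + 0.24/200) = 0.096. With 120 v 280 it is 0.105.

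**The case against.** A reader might infer that late aspirin marks severe stroke and that the contrast will therefore favour early aspirin. The documents do not support that. They say who consents when capacity is impaired, but not how long this takes. A relative may already be present, and severely affected patients may be handled faster.

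Selection can also run the other way. A patient who bleeds before dosing and so never receives aspirin is missing from the late group, while a patient dosed early who then bleeds stays in the early group. That would make late aspirin look better. Whether staff withhold aspirin in this way is itself not stated. The direction is therefore open, and the figures above illustrate the risk without estimating it.

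A reader might also infer that the trial's main conclusion is at risk. It is not. Statistical analyses makes the main analysis a single intention-to-treat comparison, and no sample-size, interim or safety provision in the article uses the timing contrast.

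Three further points for the plan deserve weight. Baseline NIHSS is collected, so an analysis plan not shown here could adjust for it or label the analysis exploratory. All analyses are to carry 95% confidence intervals, so imprecision would be visible. A prespecified direction with a stated rationale is normally a strength. None of these gives controls a value for the factor. A confidence interval does not reflect bias, and adjustment for NIHSS removes only what NIHSS measures. The article also goes beyond silence: it fixes the definition, an unadjusted method and the expected direction.

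**Conclusion.** The point holds on structure alone, without any assumed figure: the factor arises after randomisation, is undefined for controls, and leaves an observational contrast within the aspirin arm. Confounding by severity is plausible but inferred, and the documents settle neither its size nor its direction. Under the assumptions shown, spurious differences run from 3 to 12 points either way, and vanish if severity is balanced. Since only one subgroup analysis is affected and the primary comparison stands, this is of moderate severity.

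**What to change.** Redefine the subgroup by time from rt-PA bolus to randomisation. It exists in both arms and is fixed before allocation is known. Use a continuous term, or a cut chosen and justified in advance, and not a median taken from the data. Test treatment by time under intention to treat. The directional hypothesis may stay if it is attached to this factor.

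Report actual bolus-to-aspirin time for the aspirin arm only, labelled observational and exploratory, adjusted for baseline NIHSS, and not presented as evidence of a timing effect.

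The costs are small but real:

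- **Data.** The sponsor should confirm that the web-based system stores the time of randomisation. Data collection does not list it.
- **Timing of the change.** By 10 May 2010, 361 of 800 patients had been included in an open trial. The change to a predefined secondary analysis should be dated and made without sight of outcomes by arm.
- **Proxy.** Bolus-to-randomisation time only approximates when aspirin is given.
- **Power.** If the 800 patients split evenly into four cells of 200, the difference between the two risk differences has a half-width of about 1.96 × √(2 × 0.25/200 + 2 × 0.24/200) = 0.137, so the interaction test will be imprecise and should be described as such.

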### Trial size

Based on our own experience in the stroke unit cohort and the results of the rt-PA thrombolysis trials [1] and the SITS-MOST registry [23] it is expected that 50% of the patients with an ischemic stroke treated with rt-PA thrombolysis will have a poor outcome (mRS 3-6). We aim to reduce this percentage by 10%, a relative risk reduction of 20%.

A two group X^2 ^test with a 0,05 two-sided significance level will have 80% power to detect the difference between the control group proportion of 0,50 and an experimental group proportion of 0,40 (odds ratio of 0,667) when the sample size in each group is 400 (total trial size 800). With this sample size, a two-sided 95% confidence interval for the difference between the proportions will extend 0,069 from the observed difference in proportions. With this sample size we are also able to statistically detect a minimal effect size (difference between mean scores of both treatment arms divided by the SD of the control group ) of *d *= 0,20 as benchmark for assessing the relative magnitude of score differences on the continuous AMC Linear Disability Scale (ALDS) which is a secondary outcome parameter.

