### Statistical analyses

Baseline characteristics will be summarized using descriptive statistics. The main analysis of this trial consists of a single comparison between the trial medication groups of the primary outcome after three months (dichotomized Rankin score). The analysis will be based on the intention-to-treat principle. The effect size will be expressed in a relative risk (RR) estimates and absolute risk reduction (ARR). Additionally the primary outcome will be analyzed using multivariate logistic regression, adjusting (if necessary) for clinically relevant baseline imbalances. The differences between NIHSS, ALDS scores and non-dichotomized mRS will be analyzed using the two-group *t*-test, the Mann-Whitney test, linear regression and ordinal logistic regression, when appropriate. The remaining secondary outcomes will be analyzed using simple 2 × 2 tables and logistic regression. In all analyses, statistical uncertainty will be quantified via 95% confidence intervals.

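### Four overlapping, unranked ethnic contrasts roughly double the chance of a false ethnic difference; one heterogeneity test on a consistent outcome scope would serve better

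*Protocol article*

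**What the plan says.** Under Predefined subgroup-analysis, the protocol article lists the ethnic comparisons as "whites versus blacks, whites versus Hindu's, whites versus blacks and Hindu's, Hindu's versus the other ethnic groups". The specific reason comes from thrombolysis in myocardial infarction, where earlier studies are said to suggest that "racial differences do exist with an increased thrombolytic effect in blacks accompanied by an increased risk of bleeding complications". A general remark follows that the effect of adding antiplatelet therapy may vary between ethnic groups. No prediction specific to Hindus is given, and no contrast is ranked above another.

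On scope, the section opens with "With respect to the primary outcome a predefined subgroup-analyses will be performed" and closes by applying the subgroup comparisons "on primary and secondary outcome measures".

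The Statistical analyses section adds: "In all analyses, statistical uncertainty will be quantified via 95% confidence intervals". The Trial size section sets a "0,05 two-sided significance level will have 80% power" for the main comparison.

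**The concern.** Whites enter all four contrasts, and blacks and Hindus three each (in the fourth, whites and blacks are among the others). The four results are therefore several readings of the same data under different labels, with no rule for which one is the answer. Two contrasts also pool groups in a way that the specific rationale does not explain: one averages blacks with Hindus, the other puts blacks on the same side as whites.

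At stake is the credibility of a secondary claim. The section itself links ethnicity to bleeding, so a chance ethnic difference that carries the label predefined could be given undue weight. The unclear outcome scope makes it uncertain how many such looks are planned.

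**Working it through.** **Inputs.** From Trial size: poor-outcome rates of 0.50 under control and 0.40 under aspirin, and 400 patients per arm, 800 in all. From Statistical analyses: 95% intervals throughout, read here as 0.05 two-sided per contrast. From the subgroup section: the four contrasts. Two assumptions are needed. Each contrast is taken as a difference in aspirin effect between groups, and the ethnic mix is varied because the protocol states none.

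**The plan's own figure.** n per group = [1.96·√(2·0.45·0.55) + 0.842·√(0.25 + 0.24)]² / 0.10² = 388 (408 with continuity correction). With 400 per group the power is 0.813. The interval half-width is 1.96·√(0.25/400 + 0.24/400) = 0.0686, against 0,069 stated. The sample size reproduces. The protocol gives no error rate for the ethnic contrasts.

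**Redundancy.** Let w and h be the shares of whites and Hindus, and let each group's effect estimate have variance proportional to 1/share. For whites − Hindus and Hindus − all others:

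- covariance = −[1/(1−h) + 1/h] = −1/[h(1−h)]
- variances = 1/w + 1/h and 1/[h(1−h)]
- |correlation| = √{ w / [(1−h)(w+h)] }

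| Whites / Hindus | Calculation | Correlation (absolute) |
|---|---|---|
| 85% / 5% | √(0.85 / (0.95·0.90)) | 0.997 |
| 70% / 10% | √(0.70 / (0.90·0.80)) | 0.986 |
| 60% / 20% | √(0.60 / (0.80·0.80)) | 0.968 |

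The fourth contrast is close to a second copy of the second.

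**Averaging.** Suppose only blacks differ, by D. Whites versus blacks estimates D. Whites versus the two minorities combined estimates D·b/(b+h), where b is the share of blacks: 0.5 D with equal numbers, and 0.23 D to 0.77 D for 3%/10% and 10%/3% blacks/Hindus. Hindus versus others picks up D·b/(1−h): 0.05/0.95 = 0.05 D with 5% in each minority, and 0.20/0.80 = 0.25 D with 20% in each.

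**Chance of at least one false ethnic difference on one endpoint, with no true heterogeneity.**

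| Set of tests | Probability |
|---|---|
| Whites versus blacks only | 0.050 |
| Two unpooled contrasts | 0.091–0.098 |
| All four as written, normal approximation | 0.113–0.120 |
| All four, simulated binary outcome, 800 patients | 0.100–0.114 |
| One global heterogeneity test | 0.050 |
| Global test plus whites versus blacks at equal rank | about 0.08 |

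The normal-approximation rows use 1,000,000 draws per mix, with mixes from 94/3/3% to about one third each (white/black/Hindu), some with 2 to 10% in other groups. The binary simulations compare log odds ratios with a 0.5 correction, which is slightly conservative: single contrasts reject at about 0.04 to 0.05. If the four were independent, the bound would be 1 − 0.95⁴ = 0.185; overlap keeps the true figure well below that.

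**Source of the excess.** Two independent tests give 1 − 0.95² = 0.0975, and the two unpooled contrasts are close to that. The pooled pair adds about 0.02, for example 0.117 − 0.097 with 85/5/5/5%.

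**Scope.** The opening sentence limits the subgroup analyses to the primary outcome; the closing sentence extends them to the secondary outcomes. Both cannot stand.

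**The case against.** The strongest reply is that these are secondary subgroup looks. The main analysis is a single comparison, its error rate is untouched, and the protocol states no decision rule for subgroups. Looking at two minority groups separately is ordinary for a factor with several categories. Ranking and multiplicity rules may stand in an analysis plan that is not shown. The general remark about ethnic groups gives some cover for examining Hindus, and the literature cited there cannot be checked here. All of this stands, and it limits the weight of the point. It does not remove it, because the list of contrasts and the conflicting scope sentences are fixed in the protocol itself.

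A reader might infer four stronger things that the documents do not support:

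- *The white-black hypothesis is blurred.* It is not. That contrast is listed separately and estimates the full D; only the pooled contrast that includes blacks on the minority side averages it.
- *The pooled contrasts cause the doubling.* They add about 0.02; most of the excess is already there with the two unpooled contrasts.
- *The fourth contrast would turn a black-only effect into an apparent Hindu effect.* With whites at 80% or more it picks up only 0.03 D to 0.11 D. Larger shares need a mix that the protocol does not state.
- *Four contrasts on seven or eight outcomes yield 1.4 to 1.6 false positives.* That count assumes 5% rejection for every outcome. For symptomatic haemorrhage at an assumed 2 to 6% risk, with 20 to 40 black patients per arm, the white-black test rejects in only 0.06 to 1.0% of null trials. Several other outcomes are strongly related, so errors would cluster.

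**Conclusion.** The point holds as a moderate one about secondary claims. The protocol fixes four overlapping, unranked ethnic contrasts. One nearly duplicates another, and one averages the group that has a specific rationale with a group that has none. On one endpoint, the chance of at least one nominally significant ethnic difference with no true heterogeneity is about 0.10 to 0.12 instead of 0.05. This rests on an assumed ethnic mix, but it hardly moves across the mixes tried, and it reads each contrast as a 0.05 two-sided comparison of aspirin effects. The contradiction on outcome scope needs no assumption. The main comparison is not affected.

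**What to change.** In Predefined subgroup-analysis:

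1. Make one treatment-by-ethnicity heterogeneity test across the recorded categories, on the primary outcome at 0.05, the single predefined ethnic test. Report relative risk, absolute risk reduction and 95% intervals for each group.
2. Read whites versus blacks as a supporting contrast to that test, not as a second test of equal rank; at equal rank the pair gives about 0.08.
3. Delete the two pooled contrasts or label them exploratory.
4. Reconcile the opening and closing sentences on which outcomes the subgroup analyses cover. Report symptomatic intracranial haemorrhage by ethnic group descriptively, since the rationale names bleeding.

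The cost is a reworded bullet and one or two sentences, with fewer analyses and no new data. Two small downsides: the pooled contrasts lose their predefined status, and a global test is slightly less sensitive to a difference confined to one group.

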## Background

Stroke is an important cause of death and acquired disability in industrial world. In the large majority of ischemic strokes, cerebral arteries become occluded either by a cardiac embolus or by thrombus formation in atherosclerotic vessel walls. The process of thrombus formation is initiated by two separate but interacting mechanisms: fibrin formation and platelet activation. Current standard treatment in acute ischemic stroke with intravenous recombinant tissue plasminogen activator (rt-PA) aims at breaking down the fibrin cloth in order to restore recanalisation of the occluded artery. Rt-PA treatment results in an absolute 10% reduction of poor outcome compared to placebo [1]. However, benefit from this treatment rapidly declines over time after symptom onset. The number needed to treat to have 1 patient with favourable outcome is 4-5 if treatment is started within 90 minutes after symptom onset as compared to controls [2], while this number increases to 14 if treatment is started between 3 to 4.5 hours after symptom onset [2,3].

Within this current time window, early recanalisation is strongly associated with improved functional outcomes and reduced mortality [4,5]. Unfortunately, recanalisation with intravenous rt-PA is only modest. The overall recanalisation rate observed in 14 pooled intravenous thrombolysis studies was only 43% [5], partly due to re-occlusion. In continuous transcranial Doppler monitoring studies, re-occlusion occurs in 20 - 34% of rt-PA treated patients at a mean time of 65 minutes after start of treatment [6,7]. Moreover, these studies show that re-occlusion accounts for two thirds of the observed clinical deterioration after initial improvement. A recent study confirmed the association between re-occlusion and clinical deterioration and showed that early re-occlusion is highly predictive of long-term poor outcome [8].

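### The stated subgroup method, a plain comparison of the groups, does not test whether the effect of aspirin differs by onset time or ethnicity

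*Protocol article*

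**What the plan says.** All of this is in the protocol article.

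- **Scope at the start of Predefined subgroup-analysis:** "With respect to the primary outcome a predefined subgroup-analyses will be performed".
- **Subgroups listed there:** rt-PA under 2 hours, 2-3 hours or over 3 hours from symptom onset; trial medication within 1 hour or at 1-1.5 hours after the rt-PA bolus; and ethnicity, as "whites versus blacks, whites versus Hindu's, whites versus blacks and Hindu's, Hindu's versus the other ethnic groups".
- **Reasons given:** for onset time and for ethnicity, the section says that the effect of adding antiplatelet therapy may not be the same across groups. For onset time it adds that bleeding risk may also change.
- **Method, in the closing sentence:** "Subgroup analyses consist will consist of a simple comparison of these different groups on primary and secondary outcome measures".

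The Statistical analyses section defines the main analysis as one comparison between the treatment arms, with relative risk and absolute risk reduction. Its logistic regression of the primary outcome is there to adjust for baseline imbalance. No treatment-by-subgroup term appears in that section or elsewhere in the article.

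**The concern.** The reasons given for the onset-time and ethnicity subgroups concern effect modification: is the aspirin-minus-control difference the same in each group? The stated method compares the groups. It can be carried out in two ways, and neither answers that question.

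1. **Groups compared on outcome** (for example whites against blacks, arms combined). This measures whether prognosis differs.
2. **Aspirin against control within each group, separately.** This gives a set of underpowered results. Significance in one group and not in another is not evidence that the effects differ.

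At stake are statements about who benefits from early aspirin and who bleeds. Such statements could be wrong in either direction: a difference claimed where there is none, or a real one missed. The changing outcome scope and the four overlapping ethnicity contrasts leave further room for selective reading.

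This is not a detail left to an analysis plan. The article states the method, and the stated method does not fit the stated question.

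**Working it through.** **Inputs from the Trial size section.** "test with a 0,05 two-sided significance level will have 80% power to detect the difference"; "control group proportion of 0,50 and an experimental group proportion of 0,40 (odds ratio of 0,667"; "sample size in each group is 400 (total trial size 800". The article gives no risks or sizes by subgroup, so those used below are assumptions.

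**Step 1. Reproduce the plan's own figures.** With n per arm, the null standard error is SE0 = √(2 × 0.45 × 0.55 / n). The alternative standard error is SE1 = √((0.50 × 0.50 + 0.40 × 0.60) / n) = √(0.49 / n). Power is Φ((0.10 − 1.96 × SE0) / SE1).

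- At n = 400, SE0 = 0.0352, SE1 = 0.0350 and power = 0.81.
- The 95% CI half-width is 1.96 × 0.0350 = 0.069, which matches "confidence interval for the difference between the proportions will extend 0,069 from the observed difference in proportions".

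The sample size statement is sound and is not in dispute.

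**Step 2. Separate tests within groups, same true effect everywhere (0.50 v 0.40).**

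| Assumed split | n per arm in each group | Power in each group | Chance that some but not all are significant |
|---|---|---|---|
| Two halves | 200 | 0.52 | 1 − 0.52² − 0.48² = 0.50 |
| Three thirds | 133 | 0.37 | 1 − 0.374³ − 0.626³ = 0.70 |
| 20%, 50%, 30% | 80, 200, 120 | 0.24, 0.52, 0.34 | 1 − (0.244 × 0.520 × 0.343) − (0.756 × 0.480 × 0.657) = 0.72 |

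For thirds, SE0 = 0.0609 and SE1 = 0.0606, so power = Φ((0.10 − 0.1194) / 0.0606) = Φ(−0.32) = 0.37. A mixed pattern is the most likely result although the effect is identical in all groups. The unequal split shows that this does not depend on equal thirds.

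**Step 3. Groups compared on outcome, arms combined.** Assume two equal subgroups of 400 patients (200 per arm).

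- *Same effect, different prognosis.* Control risks are 0.45 and 0.55, with a 10-point aspirin effect in both. The combined risks are 0.40 and 0.50. The comparison is significant in 81% of trials, by formula and in 100,000 simulated trials. For gaps of 5, 10 and 15 points in combined risk, the rate is 30%, 81% and 99%. An interaction test on the same simulated data rejects in 4.9%, the nominal rate.
- *Different effect, same combined prognosis.* Risks are 0.55 v 0.35 in one group and 0.45 v 0.45 in the other, so effects are 20 and 0 points. Both combined risks are 0.45. The comparison of groups rejects in only 4.9% of trials; the interaction test rejects in 82%.

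**Step 4. What an interaction test can deliver at 800 patients.** With equal halves and a uniform effect, the standard error of the difference between two risk differences is √(0.49/200 + 0.49/200) = 0.070, twice the 0.035 for the overall effect. With a control risk of 0.50, power is 82% for 20 v 0 points and 30% for 15 v 5 points. If one subgroup holds 5%, 10% or 20% of patients, power for 20 v 10 points is 10%, 14% or 22%. The right test is valid but weak.

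**Step 5. Aspirin timing.** Time from rt-PA bolus to trial medication is observed only in patients given aspirin, and only after randomisation. Controls have no corresponding value, so no treatment-by-subgroup interaction can be formed.

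**The case against.** The fairest defence is that the closing sentence is garbled and loosely worded. The reasons given for onset time and ethnicity speak of the effect of adding antiplatelet therapy, and the main analysis is defined as a comparison between arms, so the authors may have meant to compare treatment effects. That is possible, but the sentence does not say so and no other section supplies the missing term. The 70% figure also depends on assumed group sizes and on someone reading the pattern of significance as heterogeneity. The article does not announce that reading, and it quantifies uncertainty by confidence intervals. The figure is therefore an illustration.

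Three stronger claims are tempting, and the article does not support them.

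- **A known prognosis gap between time groups.** A reader might take "The number needed to treat to have 1 patient with favourable outcome is 4-5 if treatment is started within 90 minutes" with the figure of 14 for 3-4.5 hours and subtract the reciprocals: 20-25 points less 7 points gives 13-18 points. Those figures are rt-PA benefits against untreated controls within each window. They give an outcome gap between early and late patients only if control prognosis is equal in both windows, which is not stated. The windows (90 minutes, 3-4.5 hours) are also not the subgroup cut-points.
- **A count of false positives.** A reader might multiply contrasts by outcomes to reach dozens of tests. The onset-time item is one three-way comparison, no significance threshold is set for subgroups, and the outcome scope is itself unclear. No firm count follows.
- **A threat to the trial's conclusion.** The main analysis is a single comparison of the primary outcome, and the article ties neither the sample size nor the interim decisions to the subgroups.

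Two points about the remedy also stand. The article does not say that the effect changes steadily with time, so an ordered trend test would be a preference. The article itself raises bleeding risk over time, so dropping bleeding altogether would discard one of its own reasons.

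**Conclusion.** The point holds in a limited form. For onset time and ethnicity, the stated method does not answer the stated question under either available reading. With a uniform effect, separate tests give a mixed pattern in about 50% of trials with two equal groups and about 70% with three. Comparing groups on outcome can be significant in 81% of trials without effect modification and can miss a 20 v 0 point difference almost entirely. The uniform effect comes from the plan; the group sizes and subgroup risks are assumptions.

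The section's outcome scope contradicts itself, and the four ethnicity contrasts overlap. These are defects of wording that one revision can settle.

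The correction is worth making but ranks below a mandatory one, because the primary analysis is untouched. Since interaction power is low, the subgroup results would be exploratory in any case.

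**What to change.** Replace the closing sentence of Predefined subgroup-analysis with text to this effect:

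- **Onset-to-bolus time and ethnicity:** a treatment-by-subgroup interaction analysis, with time in its three existing strata and ethnicity as one overall interaction in place of the four overlapping contrasts. Report the treatment effect within each subgroup and the interaction estimate, each with a 95% confidence interval, labelled exploratory.
- **Outcome scope:** the primary outcome, stated once, with SICH and serious bleeding by subgroup shown descriptively.
- **Aspirin timing:** a descriptive, non-randomised comparison within the aspirin arm, with no interaction test.

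The cost is analysis wording only. Data collection, conduct and sample size do not change. The Discussion reports 361 of 800 patients included, so on that count the text can be settled before the final analysis.
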